### Recruitment {15}

Patients who are about to have PLIF with general anesthesia and meet the inclusion criteria will be recruited through multimodal strategies, including advertisements in hospital social media (WeChat) and newspapers, publicity at community service centers, and a clinical patient database. Informed consent will be obtained before randomization. The schedule of enrolment, intervention, and assessments is shown in Fig. 2.

### Assignment of interventions: allocation

#### Sequence generation {16a}

Eligible patients will be randomly assigned to the treatment group or control group in a 1:1 ratio using a central web-based randomization tool. A block randomization sequence using a web-based allocation system will be generated by a central randomization system (http://124.205.181.142:8082/xwtf/).

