## Introduction

### Background and rationale {6a}

Postoperative nausea and vomiting (PONV) are some of the most common and undesirable side effects of conventional anesthesia surgery [1–3]. The incidence of PONV after general anesthesia may reach as high as 30~50% [4]. PONV could also lead to serious complications, such as hematoma, surgical incision hemorrhage, pulmonary aspiration, wound dehiscence, and dehydration, aspiration pneumonia, and increased intracranial pressure [5–8]. On the other hand, PONV was likely to reduce patients’ satisfaction, delay discharge and recovery, and increase medical costs [9, 10]. Therefore, unignorable complication still poses a severe challenge for anesthesiologists, clinicians, and researchers.

Existing consensus guidelines from the American Society for enhanced recovery (ASER) recommended a variety of medications that worked at different receptor sites, such as antihistamines, steroids, and so on [11]. However, no single antiemetic drug could fully respond to prophylaxis and management of PONV, and high-risk individuals often did not receive appropriate antiemetic prophylaxis [12]. Besides, traditional drug therapy had its obvious side effects, while the costs of new agents including NK1-antagonists or the newer 5-HT3 antagonists became relatively higher [13, 14]. On the contrary, more and more turned to alternative and complementary medicine, including herbal medications, acupressure, and so on [15–17].

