## Methods: participants, interventions, and outcomes

### Study setting {9}

The patients will be recruited from the orthopedic inpatient department from the three affiliated hospitals of China Academy of Chinese Medical Sciences, including Wangjing Hospital, Xiyuan Hospital, and Guanganmen Hospital.

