### Sample size {14}

A relatively small number of clinical trials has investigated the effects of acupoint plaster on PONV; however, the research results are not appropriate to calculate the sample size for this study. The sample size is calculated based on the primary endpoint. The small sample-size clinical practice suggests the decreased rate of nausea and vomiting frequency is 60% in the treatment group, while the rate is 40% in the control group based on previous literature. According to the superiority test, it is estimated that at least 69 participants per group are needed when the study achieves 90% power and a two-sided 5% significance level. Given the dropout rate to 20%, the sample size in the clinical trial sets at a total of 166 cases, and each group is 83 cases.

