### Statistical methods

#### Statistical methods for primary and secondary outcomes {20a}

The efficacy and safety analysis will be conducted according to the intention-to-treat principle. As the third party, the statistical analysis will be performed by the Institute of Clinical Basic Medicine, China Academy of Chinese Medical Sciences, using the statistical packages of social sciences software (SPSS; version 19.0). All the results are based on two-sided tests. Continuous data will be presented as means and standard deviations and compared using the independent *t* test or Wilcoxon’s rank-sum test. On the other hand, categorical data will be presented as percentages and frequencies and analyzed using the chi-square or Fisher’s exact test. The missing values will be implemented by the method of multiple imputations. A *p* value less than or equal to 0.05 will be considered statistically significant.

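### The planned test of PONV occurrence leaves hospital out in a three-hospital trial, which can cost a little efficiency; a hospital-stratified test is a minor, optional improvement

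*Protocol article*

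**What the plan says.** All references are to the protocol article.

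- **Study setting {9}:** patients come from "the three affiliated hospitals of China Academy of Chinese Medical Sciences".
- **Sequence generation {16a}:** "A block randomization sequence using a web-based allocation system will be generated by a central randomization system". Block size and strata are not given. Under Implementation {16c}, practitioners from the different units obtain their allocations from this system.
- **Statistical methods {20a}:** "categorical data will be presented as percentages and frequencies and analyzed using the chi-square" or Fisher's exact test. Continuous data get a t test or rank-sum test. No hospital term or covariate appears, and "All the results are based on two-sided tests".
- **Additional analyses {20b}:** none are planned.
- **Outcomes {12}:** the primary outcome covers both the first occurrence and the frequency of PONV over 48 hours. Occurrence is categorical, so the chi-square or Fisher test would apply to it.

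**The concern.** When patients are recruited in several hospitals and the event rate varies between them, part of the outcome variation is variation between hospitals. An unadjusted two-group test counts that variation as noise. What this costs depends on how allocation was done:

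- **One shared sequence.** Blocks balance the total, not each hospital. The arms can differ by chance in their hospital mix, and the unadjusted test leaves this in the error term. It is still valid, but less precise.
- **Blocks within hospital.** The design has already removed the between-hospital variation from the treatment comparison, but the unadjusted test still charges for it. Its standard error is then too large and the test is conservative.

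In either case, if hospitals differ, a hospital-stratified test uses the data better. What is at stake is a few points of power in a trial with none to spare, not the validity of the result.

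**Working it through.** **Inputs from the plan.** 166 patients, 83 per arm, 1:1; three hospitals; two-sided 5%; rates of 60% and 40% (Sample size {14}). The analysis is by intention to treat with multiple imputation, so 83 per arm is the relevant number.

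**Assumptions (not in the documents).** Equal recruitment by hospital, blocks of 4, control rates by hospital as listed below, and a common odds ratio of (0.60/0.40)/(0.40/0.60) = 2.25.

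**Step 1: the plan's own figure.** The plan states no figure that involves hospital. Its sample size is "at least 69 participants per group are needed when the study achieves 90% power". The usual formula gives

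n = [1.960 × √(2 × 0.5 × 0.5) + 1.282 × √(0.24 + 0.24)]² / 0.20² = (1.386 + 0.888)² / 0.04, which rounds up to 130 per group.

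So 69 does not reproduce. At 83 per arm, power is Φ[(0.20 − 1.960 × √(0.50/83)) / √(0.48/83)] = Φ(0.63) = 74%. That shortfall is a separate and much larger matter. Here the 74% serves only as a benchmark for the simulation.

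**Step 2: simulation.** 5,000 trials per setting, comparing the unadjusted chi-square with Cochran-Mantel-Haenszel (CMH) by hospital. Simulation error is about 0.7 points for power and √(0.05 × 0.95/5000) = 0.3 points for type I error.

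| Control rates by hospital | Allocation | Type I error: unadjusted / CMH | Power: unadjusted / CMH | Change in power |
|---|---|---|---|---|
| 40/40/40% | shared | 4.7% / 4.5% | 74.1% / 72.9% | −1.2 |
| 40/40/40% | by hospital | 5.4% / 5.4% | 74.7% / 74.7% | 0.0 |
| 30/40/50% | shared | 4.3% / 4.6% | 69.7% / 70.4% | +0.7 |
| 30/40/50% | by hospital | 5.1% / 5.2% | 71.9% / 72.3% | +0.4 |
| 20/40/60% | shared | 4.9% / 4.7% | 64.1% / 68.3% | +4.2 |
| 20/40/60% | by hospital | 3.8% / 4.8% | 64.5% / 68.2% | +3.7 |

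The first row agrees with the 74% from step 1. In log-odds relative to 40%, the 20/40/60% setting has offsets of −0.98, 0 and +0.81.

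**Step 3: hand check of the conservative case.** Take stratified allocation, no treatment effect, and rates of 20/40/60%.

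- Variance used by the chi-square: 0.40 × 0.60 = 0.24.
- Variance that actually applies, within hospital: (0.16 + 0.24 + 0.24)/3 = 0.213.
- Ratio 0.213/0.24 = 0.889, with square root 0.943.
- True type I error = 2 × [1 − Φ(1.960/0.943)] = 2 × [1 − Φ(2.08)] = 3.8%, as simulated.

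**Step 4: a second set of assumptions.** With PONV occurrence of 45% v 25% and a shared sequence, power for unadjusted v CMH is 77% v 77% with no hospital difference, 76% v 77% at offsets of ±0.5, and 69% v 73% at ±0.85. With stratified allocation at ±0.85, type I error is 3.6% unadjusted and 4.8% with CMH. The size is the same.

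**The case against.** The strongest reply is that nothing here is wrong. Under a shared sequence the unadjusted test keeps its error rate (4.3% to 4.9% above), because chance imbalance between hospitals is already part of that rate. This stands.

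The gain may also be close to nil. The upper end needs offsets of about ±0.85, which around a 40% rate means roughly 22% in one hospital and 61% in another. The article points the other way: the hospitals belong to one academy, every patient gets the same antiemetic at the end of surgery and practitioners are trained to a common standard (Intervention description {11a}), and anaesthesia and postoperative care are to be uniform (Relevant concomitant care {11d}). This stands too and limits the size. It does not make the unadjusted test preferable.

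A reader might infer two stronger points, and the documents support neither:

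- **That allocation was not stratified by hospital.** Sequence generation {16a} uses the singular and names no stratum, but it does not say that there is none. A condensed article may leave this to the full protocol, and practitioners drawing from one system is compatible with separate lists per hospital. Restratifying is also a poor remedy, since recruitment began on 18 May 2018 (Trial status).
- **That adjusting for patient risk would gain much more.** Eligibility restricts age to 30 to 65, BMI to 20 to 25 and ASA grade to I or II, and nothing says how well these predict PONV. The background's remark that "high-risk individuals often did not receive appropriate antiemetic prophylaxis" names no risk factor. A larger gain would need a risk score whose strength is purely assumed.

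**Conclusion.** This is a minor, optional efficiency improvement. The plan commits to an unadjusted test where a hospital-stratified one is at least as good whenever hospitals differ appreciably. At 83 per arm the difference is about 0 to 4 points of power over assumed offsets of 0 to ±0.85 in log-odds. If hospitals do not differ at all, there is nothing to gain, and under a shared sequence perhaps a point to lose. If allocation is stratified and the spread is at its largest, the unadjusted type I error is about 4% instead of 5%.

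These figures rest on assumed hospital rates, equal recruitment, small blocks and a common odds ratio. The direction does not depend on which allocation scheme was used. The planned test is not invalid, and adjusting for hospital would not repair the sample-size shortfall.

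**What to change.** In Statistical methods {20a}, replace the unadjusted test of PONV occurrence with a Cochran-Mantel-Haenszel test stratified by hospital. A logistic model with hospital as a factor is an alternative; age and ASA grade may be added only if they are fixed before unblinding. Include hospital in the analysis of PONV frequency as well. The unadjusted comparison can be kept as a supporting result.

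The cost is a few lines of text and slightly more analysis work. No patients, visits or data are added, since the recruiting hospital is known for every patient. The change works under either allocation scheme and can still be made after recruitment has begun, provided it is fixed before unblinding.

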#### Concealment mechanism {16b}

The system is managed by an independent statistician (the Institute of Clinical Basic Medicine, China Academy of Chinese Medical Sciences, China), who is not involved in the implementation of statistical analysis of the trial.

#### Implementation {16c}

Three practitioners from the different units will apply for the random number from the randomization system and treatment allocation is determined based on the web the day before the operation.

#### Assignment of interventions: blinding

##### Who will be blinded {17a}

All the plasters used in the RCT have a similar appearance, smell, and size to ensure the practitioners and patients impossible to distinguish the treatment allocation. Furthermore, the plasters will be packed and labeled to ensure that the researchers and the subjects involved in the study will remain fully blinded as to the identity of the treatment administered. Outcome assessors, laboratory technicians, data managers, and statisticians will not know the treatment allocations, which will be revealed at the end of the trial.

##### Procedure for unblinding if needed {17b}

In case of an emergency, the researcher shall open it according to the procedures specified in the test plan. Once the case number is opened, the trial will be suspended, and the researcher shall record the reason for suspension in the case report form.

#### Data collection and management

##### Plans for assessment and collection of outcomes {18a}

The whole research team including the investigators, research assistants, and research nurses will be required to attend the professional training before recruitment. It is beneficial to ensure the researchers are familiar with the trial administration process and strictly adhere to the study protocol.

### Plans to promote participant retention and complete follow-up {18b}

The data collected in this trial will comprise information recorded in the case report forms. Data quality will be checked regularly by research assistants and overseen by monitors. Data monitoring will be conducted regularly with standard operating procedures. All the data modifications are to be marked in the case report forms. If participants withdraw from the trial during the study period, the reasons must be documented and the dropout rate is counted.

### Data management {19}

Data management was handled by the Institute of clinical basic medicine, China Academy of Chinese Medical Sciences. All the trial data are collected through strict verification and management; the database will be locked after all data have been cleaned. And the data are put into an Epidata 3.1 database by two researchers independently. A consistency test is conducted between the database.

### Confidentiality {27}

Both paper files and electronic data will be preserved for at least 5 years after publication. If readers and reviewers have any questions, they can contact the corresponding author for access to the original data. Patient information will remain anonymous, including name, ID number, and telephone number. The management department of the research institute or members of the ethics committee will review the progress of the trial after 3 months, independently of the researchers, and decide if premature closure of the study is required, based solely on adverse events.

### Plans for collection, laboratory evaluation, and storage of biological specimens for genetic or molecular analysis in this trial/future use {33}

Not applicable. The remaining blood samples will be treated as abandoned blood after the test.

### Statistical methods

#### Statistical methods for primary and secondary outcomes {20a}

The efficacy and safety analysis will be conducted according to the intention-to-treat principle. As the third party, the statistical analysis will be performed by the Institute of Clinical Basic Medicine, China Academy of Chinese Medical Sciences, using the statistical packages of social sciences software (SPSS; version 19.0). All the results are based on two-sided tests. Continuous data will be presented as means and standard deviations and compared using the independent *t* test or Wilcoxon’s rank-sum test. On the other hand, categorical data will be presented as percentages and frequencies and analyzed using the chi-square or Fisher’s exact test. The missing values will be implemented by the method of multiple imputations. A *p* value less than or equal to 0.05 will be considered statistically significant.

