##### Experimental group

The patients in the experimental group will receive a 2-day AHP plus conventional Torasetron hydrochloride therapy. Treatment procedures in sequential order are to locate the acupoints, disinfect the skin, and attach the plaster on the skin over the acupoints. It must be removed immediately if an allergic reaction occurs, which may be described by patients as a burning sensation, severe itchiness, blisters, pruritus, or rash on the local skin. A total of 2 sessions will be performed 24 h and 48 h after the operation. The treatment starts before anesthesia before the operation, with at most 6 h of treatment twice per day.

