### Outcomes {12}

#### Primary outcome

##### The first occurrence and frequency of PONV

The primary outcome will be recorded within the postoperative 48 h. The important index will be self-reported daily and recorded in a diary during the treatment course. In the meantime, each participant will be face-to-face interviewed to attend an in-person assessment at the orthopedic inpatient department.

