### Methods in analysis to handle protocol non-adherence and any statistical methods to handle missing data {20c}

Sensitivity analysis was used for the lost causes, and the results of the last observation carried forward or the baseline observation carried forward were used for the sensitivity analysis of the measurement data. The sensitivity analysis of the counting data includes the analysis of the cases in the experimental group and the control group as the ineffective treatment and the best/worst case. In the worst-case analysis, the control group was treated successfully and the experimental group was treated as a failure.

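### Safety is put under intention-to-treat, so randomised patients who never wear a plaster count in the skin-reaction denominator (minor)

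*Protocol article*

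**What the plan says.** Under Statistical methods for primary and secondary outcomes {20a}, one rule covers both kinds of analysis: "The efficacy and safety analysis will be conducted according to the intention-to-treat principle". The same section says of missing data: "The missing values will be implemented by the method of multiple imputations". It makes no separate statement for adverse events.

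On timing, Implementation {16c} says that "treatment allocation is determined based on the web the day before the operation", and the Experimental group section says "The treatment starts before anesthesia before the operation". The latter section also describes two sessions at 24 h and 48 h after surgery. On either description, exposure to the plaster begins after allocation.

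The Safety assessment section and Adverse event reporting and harms {22} single out skin lesions, with urticaria and pruritus as examples, as the reactions to watch for. The article describes no other safety population.

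**The concern.** Intention-to-treat protects the randomised comparison of efficacy. It answers a different question from the one usually asked of local safety, which is how often people who wear this plaster react to it. A patient who never wears a plaster cannot have a plaster reaction, so keeping that patient in the denominator can only lower the reported rate. A patient who was given the other arm's plaster contributes any reaction to the product that did not cause it.

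At stake is the accuracy of the skin-reaction rate for each plaster. The error from untreated patients has a fixed direction, toward reporting less harm. Because the safety population is stated outright, this is not a detail left open for a later analysis plan: a plan that defined safety by plaster received would contradict the published sentence.

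**Working it through.** The article gives no skin-reaction rate and no expected number of untreated patients, so there is no safety figure of the plan's own to reproduce. What can be checked is how the stated rule behaves.

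**Inputs**
- Patients randomised per arm: 83 (Sample size {14}).
- Untreated patients per arm, *k*: not given. Assumed 1, 2, 4 or 8, that is 1.2%, 2.4%, 4.8% or 9.6% of 83.
- Reaction rate among patients who wore a plaster, *r*: not given. Assumed 5%, 10% or 20%.
- Outer bound: Sample size {14} allows 20% dropout. If all of it were patients never treated, *k* would be 17 (0.20 × 83 = 16.6).

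**Step 1: untreated patients.** Reactions arise only among the 83 − *k* treated patients but are divided by 83:

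reported rate = *r* × (83 − *k*) / 83

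| *k* | (83 − *k*)/83 | *r* = 5% | *r* = 10% | *r* = 20% |
|---|---|---|---|---|
| 0 | 1.000 | 5.0% | 10.0% | 20.0% |
| 1 | 0.988 | 4.9% | 9.9% | 19.8% |
| 2 | 0.976 | 4.9% | 9.8% | 19.5% |
| 4 | 0.952 | 4.8% | 9.5% | 19.0% |
| 8 | 0.904 | 4.5% | 9.0% | 18.1% |
| 17 (bound) | 0.795 | 4.0% | 8.0% | 15.9% |

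The relative understatement equals the untreated share. For a 10% rate it is 0.1 to 1.0 percentage points over the assumed range, and 2.0 points at the bound.

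**Step 2: no reactions seen.** The one-sided 95% upper limit for 0 events in *n* patients is 1 − 0.05^(1/*n*). With *n* = 83 it is 3.5%. With *n* = 79 treated it is 3.7%, with 75 treated 3.9%, and at the bound of 66 treated 4.4%. Using 83 makes the reassurance look slightly firmer than the exposure supports.

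**Step 3: comparison between arms.** If *k* is the same in both arms, the factor (83 − *k*)/83 cancels from the risk ratio, which is unchanged. The risk difference shrinks by that factor.

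**Step 4: wrong plaster.** If *m* patients in each arm wore the other arm's plaster, the difference between arms is multiplied by 1 − 2*m*/83. With *m* = 1, purely as an illustration, that is 1 − 2/83 = 0.976. The documents describe no such error and give no rate for one.

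**The case against.** The strongest reply is that the effect is small and hypothetical. Allocation is only one day before surgery, so few patients are likely to go untreated; with 1 to 4 of 83, a 10% rate still reads 9.9% to 9.5%. If the untreated share is similar in both arms, the risk ratio does not move. Plasters are packed and labelled, and nothing suggests that mis-dispensing is expected. Each adverse event is recorded with its timing, severity, management and causality and is followed to resolution. The decision on early closure described under Confidentiality {27} rests on adverse events. A larger denominator removes no event from these records. All of this stands, and it is why the point is minor. It does not answer the point itself, because the reported rate would still rest on a population that includes people who were not exposed.

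A reader might go further and infer that patients whose operation is cancelled will be given an imputed nausea and vomiting outcome, or be scored as success or failure in the sensitivity analyses under {20c}. It is true that "The primary outcome will be recorded within the postoperative 48 h", and such a patient has no postoperative period. But the article never mentions cancelled surgery, makes the fusion operation under general anaesthesia an eligibility criterion, and may leave the handling of such patients to the full protocol or analysis plan. Any loss of effect in the worst-case analysis would be a feature of that deliberately extreme analysis for missing data of every kind, not of this problem.

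A reader might also infer that adverse events will be imputed. The general missing-data sentence does not exclude it, but nothing says that it is intended.

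**Conclusion.** The point holds for safety only and is minor. The article's stated rule, taken with allocation before exposure, keeps unexposed patients in the skin-reaction denominator and files any reaction to a wrongly given plaster under the other product. The understatement from untreated patients equals their share of the arm: a 10% rate reported as 9.9% to 9.0% if 1 to 8 of 83 per arm are untreated, 8.0% if the whole dropout allowance were never treated, and no effect if all are treated. Both the reaction rate and the untreated numbers are assumptions, since the documents give neither.

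The documents do not support saying that the rule conceals adverse events, because individual recording and review are unaffected. Nor do they support a criticism of intention-to-treat for efficacy.

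**What to change.** In Statistical methods {20a}, keep intention-to-treat for efficacy and replace the safety half of the sentence with wording along these lines: safety will be analysed in all participants who received at least one plaster, grouped by the plaster actually received, and adverse events will not be imputed. Reporting, by arm, how many randomised patients received no plaster would show how much the two populations differ.

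The cost is one reworded sentence and a second analysis set. The small downside is that a comparison between arms in this set is not strictly randomised, so it should be read as descriptive of exposed patients.

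The change should not be extended to an efficacy set restricted to patients who start anaesthesia. The article has treatment starting before anaesthesia, so a reaction could lead to withdrawal in that interval. Exclusion could then depend on the paste worn, even with staff blinded.

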##### Quality of life

The quality of life will be self-administered using the functional assessment of the SF-12 questionnaire at pre-operation, postoperative 24 h and 48 h. The SF-12 questionnaire measures 12 items, which can be classified as a physical and mental component [25].

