##### Blood tests

Blood samples will be collected at pre-operation and postoperative 24 h to measure the levels of serological indicators. The fasting venous blood will be drawn and centrifuged, the separated serum is stored at a – 80 °C refrigerator. Gastric secrete elements and 5-hydroxytryptamine will be analyzed in the research laboratory of Beijing North Biotechnology every week.

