## Methods for additional analyses (e.g., subgroup analyses) {20b}

Not an applicant.

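### SF-12 and serum markers are measured before surgery, but the named t or rank-sum test is less efficient than a baseline-adjusted comparison (secondary outcomes only)

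*Protocol article*

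**What the plan says.** The protocol article's section on statistical methods for primary and secondary outcomes {20a} gives one rule for all continuous data: "Continuous data will be presented as means and standard deviations and compared using the independent" t test or Wilcoxon's rank-sum test. It names no covariate. It does not say whether the quantity tested is the post-operative value or the change from before surgery.

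Two groups of secondary outcomes have a pre-operative measurement:

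- Quality of life: "SF-12 questionnaire at pre-operation, postoperative 24 h and 48 h". The section divides the instrument into a physical and a mental component.
- Serology: "Blood samples will be collected at pre-operation and postoperative 24 h to measure the levels of serological indicators", covering gastric secretion markers and 5-hydroxytryptamine.

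The baseline value is mentioned in the analysis only in section {20c}, as one of two carry-forward rules in a sensitivity analysis for missing measurements. Multiple imputation is specified in {20a} without a list of predictors. The entry for additional analyses {20b} reads "Not an applicant", evidently meaning not applicable.

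**The concern.** A measurement taken before surgery usually explains part of the variation in the same measurement taken afterwards. A two-sample test on post-operative values leaves that part in the error term, so a chance difference between the arms at baseline passes into the estimated treatment effect and widens its uncertainty. A test on changes does use the baseline, but with a fixed slope of one, which over-corrects whenever the correlation is modest. ANCOVA estimates the slope from the data.

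At stake is the precision of the SF-12 and serum comparisons. Each patient already gives a pre-operative blood sample and completes a pre-operative questionnaire, so the information is available at no further cost.

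**Working it through.** **Plan's own figure.** There is none to reproduce. The article gives no effect size, standard deviation, correlation or power for the SF-12 or the serum markers.

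**Inputs.**
- Test: independent t or rank-sum ({20a}).
- Measurement times: SF-12 before surgery, 24 h and 48 h (Quality of life); serum before surgery and 24 h (Blood tests).
- Patients: 69 per group, from Sample size {14}. That figure was set for the primary endpoint and serves here only as a convenient number of evaluable patients.
- Two-sided 5% level ({20a}, {14}).
- Correlation r between pre- and post-operative values: not given, so assumed over a range.

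**Formulas.** Take the variance of a post-operative value as 1, the same before and after surgery and in both arms. The variance entering the comparison is then:
- post-operative values: 1
- change from baseline: 2(1 - r)
- ANCOVA: 1 - r²

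The ratio of ANCOVA to change is (1 - r²) / [2(1 - r)] = (1 + r)/2, which is below 1 for any r below 1. ANCOVA is therefore at least as precise as either alternative, apart from the one degree of freedom it spends out of 2 × 69 - 2 = 136.

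**Reference effect.** The difference that the unadjusted t test detects with 80% power at 69 per group is (1.96 + 0.84) × √(2/69) = 0.477 SD. For that same difference, power under variance v is Φ(2.80/√v - 1.96).

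| Assumed r | ANCOVA variance 1 - r² | Fall in standard error | Equivalent unadjusted n per group, 69/(1 - r²) | Power, post-operative values | Power, change | Power, ANCOVA |
|---|---|---|---|---|---|---|
| 0.2 | 0.96 | 2.0% | 72 | 80.0% | 60.1% | 81.6% |
| 0.3 | 0.91 | 4.6% | 76 | 80.0% | 65.8% | 83.6% |
| 0.5 | 0.75 | 13.4% | 92 | 80.0% | 80.0% | 89.9% |
| 0.7 | 0.51 | 28.6% | 135 | 80.0% | 95.1% | 97.5% |

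**Reading.** ANCOVA is the best of the three in every row. Against post-operative values the gain is negligible at r = 0.2, small at 0.3 and material from about 0.5. Against change scores the gain is largest where r is low, and below r = 0.5 a change score does worse than ignoring the baseline altogether. These figures are for the t test; no separate figure was computed for the rank-sum test.

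**The case against.** The strongest reply is that nothing here is wrong. An unadjusted comparison is valid under randomization, no other section contradicts {20a}, and covariates are often left to an analysis plan, which is not shown. Validity is conceded in full. The reply about the unseen plan stands in part: the entry under {20b} gives subgroup analyses as its example and does not settle which covariates the main comparison uses. But {20a} does not leave the method open. It names two tests, and neither can take a covariate.

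The size of the gain is also open to challenge. No correlation is given, and a major operation lies between the two measurements, so a high r cannot be presumed. That stands, and it is why a range is shown.

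Several stronger readings are tempting, but the article does not support them:

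- *That baseline values are not used at all.* A t test on change is not excluded, {20c} uses baseline in a sensitivity analysis, and the imputation predictors are not restricted.
- *That the analysis must include hospital.* Patients come from "the three affiliated hospitals of China Academy of Chinese Medical Sciences", but the article describes blocked randomization without stating stratification by hospital, so there is no stated design feature to match. The gain would also be small. For the same reference effect, power goes from 80.0% to 80.4%, 82.0% and 84.0% at assumed intraclass correlations of 0.01, 0.05 and 0.10. Nor would adding hospital to a logistic model for the nausea and vomiting proportion generally shrink the standard error of the odds ratio, and it changes the odds ratio being estimated.
- *That testing SF-12 separately at 24 h and 48 h is an error.* Separate testing is an inference, and each single-time comparison would still be valid.
- *That adjustment would help the trial reach its stated power.* Section {14} bases the sample size on the primary endpoint, a comparison of 60% with 40%. Adjusting SF-12 or serum values does nothing for it.

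**Conclusion.** The point holds as a matter of efficiency for secondary outcomes. The article fixes a valid but generally less precise method for outcomes whose pre-operative value is already collected. Relative to a test on post-operative values, ANCOVA reduces the variance by 9%, 25% and 49% at r = 0.3, 0.5 and 0.7, and by only 4% at r = 0.2. Relative to a test on changes, the reduction is (1 - r)/2, that is 35%, 25% and 15% at r = 0.3, 0.5 and 0.7.

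These sizes rest on assumed correlations, equal variances before and after surgery and between arms, and a linear relation. The direction does not depend on the particular r chosen, but the practical importance does. No bias is corrected and no conclusion about the primary endpoint changes. It is a worthwhile improvement and not a defect that threatens the trial.

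**What to change.** In {20a}, replace the two-sample test for these outcomes as follows:

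- Serum markers at 24 h: ANCOVA with treatment group and the pre-operative value of the same marker as covariate. Because {20a} itself allows for a rank-sum test, state in advance how skewed markers are handled, either by log-transforming both the pre- and post-operative values or by a rank-based ANCOVA.
- SF-12 physical and mental component scores at 24 h and 48 h: ANCOVA at each time with the pre-operative component score as covariate. A repeated-measures mixed model covering both times is an option and not a requirement.

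The cost is a few sentences. No new data are needed, and the methods can be run in the statistical software that {20a} names. Fixing the covariate before unblinding also removes any later choice between adjusted and unadjusted results.
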